### **7.2.1. Dose levels**

Table 1:

| DRUG        | Units | STARTING DOSE | LEVEL |     |            |                  |                  |
|-------------|-------|---------------|-------|-----|------------|------------------|------------------|
|             |       |               | -2    | -1  | 0
START | +1               | +2               |
| Imatinib    | mg    | 400           | 200   | 300 | 400        | 600 a | 800 a |
| Regorafenib | mg    | 160           | 80    | 120 | 160        | ----             | ----             |

- a. Only patients with *KIT* exon 9 mutations are permitted to have imatinib dose escalations above 400mg.

**In Arm A** (standard therapy arm), dose modifications for adverse events thought to be related to imatinib are shown below:

Table 2:

| Toxicity         | Grade 1                         | Grade 2                         | Grade 3                                                                                                                                                                                                                                                            | Grade 4                                                                                                                                                             |
|------------------|---------------------------------|---------------------------------|--------------------------------------------------------------------------------------------------------------------------------------------------------------------------------------------------------------------------------------------------------------------|---------------------------------------------------------------------------------------------------------------------------------------------------------------------|
| Non-haematologic | Continue at the same dose level | Continue at the same dose level | Withhold dose until toxicity is grade $\leq 1$ , then resume at same dose level. If event recurs, withhold dose until toxicity is grade $\leq 1$ and reduce dose for next cycle by 1 level. Dose reduce by 1 further level for further grade 3 or higher toxicity. | Withhold dose until toxicity is grade $\leq 1$ , then reduce dose for next cycle by 1 level. Dose reduce by 1 further level for further grade 3 or higher toxicity. |

## ALT GIST

|                                     |                                  |                                 |                                                                                                                                                                                                                                                                                                                              |                                                                                                                                                                                          |
|-------------------------------------|----------------------------------|---------------------------------|------------------------------------------------------------------------------------------------------------------------------------------------------------------------------------------------------------------------------------------------------------------------------------------------------------------------------|------------------------------------------------------------------------------------------------------------------------------------------------------------------------------------------|
| Haematologic (excluding anaemia **) | Continue at the same dose level. | Continue at the same dose level | Withhold dose until neutrophils $\geq 1.0$ and platelets $\geq 100$ , then resume treatment at the same dose level. If event recurs, withhold dose until neutrophils $\geq 1.0$ and platelets $\geq 100$ , and reduce dose for next cycle by 1 level. Dose reduce by 1 further level for further grade 3 or higher toxicity. | Withhold dose until neutrophils $\geq 1.0$ and platelets $\geq 100$ , then reduce dose for next cycle by 1 level. Dose reduce by 1 further level for further grade 3 or higher toxicity. |
|-------------------------------------|----------------------------------|---------------------------------|------------------------------------------------------------------------------------------------------------------------------------------------------------------------------------------------------------------------------------------------------------------------------------------------------------------------------|------------------------------------------------------------------------------------------------------------------------------------------------------------------------------------------|

\*\*No dose modifications are required for Grade 1–4 anaemia however transfusion is permitted.

**In Arm B** (alternating therapy arm) for events specifically related to regorafenib (skin toxicity, treatment emergent hypertension, and hepatic dysfunction), see tables below:

Dose modifications for skin toxicity including Hand-foot skin reaction.

Table 3:

| Skin Toxicity Grade                                                                                                                                                                 | Occurrence                                     | Dose Modification a                                                                                                                                                                            |
|-------------------------------------------------------------------------------------------------------------------------------------------------------------------------------------|------------------------------------------------|-----------------------------------------------------------------------------------------------------------------------------------------------------------------------------------------------------------|
| Grade 1: Numbness, dysaesthesia, paraesthesia, tingling, painless swelling, erythema or discomfort of the hands or feet which does not disrupt the participant's normal activities. | Any                                            | Maintain dose level and immediately institute supportive measures for symptomatic relief.                                                                                                                 |
| Grade 2: Painful erythema and swelling of the hands or feet and/or discomfort which affects the participant's normal activities.                                                    | 1st occurrence                                 | Decrease dose by one dose level and immediately institute supportive measures. If there is no improvement, interrupt therapy for a minimum of 7 days, until toxicity resolves to Grade 0-1 c . |
|                                                                                                                                                                                     | No improvement within 7 days or 2nd occurrence | Interrupt therapy until toxicity resolves to Grade 0-1. When resume treatment, decrease dose by one dose level c .                                                                             |
|                                                                                                                                                                                     | 3rd occurrence                                 | Interrupt therapy until toxicity resolves to Grade 0-1. When resume treatment, decrease dose by one additional dose level b,c .                                                                |
|                                                                                                                                                                                     | 4th occurrence                                 | Discontinue study treatment permanently.                                                                                                                                                                  |
| Grade 3: Moist desquamation, ulceration, blistering or severe pain of the hands or feet, or severe discomfort that causes the                                                       | 1st occurrence                                 | Institute support measures immediately. Interrupt therapy for a minimum of 7 days until toxicity                                                                                                          |

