## ALT GIST

|                                                                         |                |                                                                                                                                                                                                          |
|-------------------------------------------------------------------------|----------------|----------------------------------------------------------------------------------------------------------------------------------------------------------------------------------------------------------|
| participant to be unable to work or perform activities of daily living. |                | resolves to Grade 0-1. When resume treatment, decrease dose by one dose level.                                                                                                                           |
|                                                                         | 2nd occurrence | Institute support measures immediately. Interrupt therapy for a minimum of 7 days until toxicity resolves to Grade 0-1. When resume treatment, decrease dose by one additional dose level b . |
|                                                                         | 3rd occurrence | Discontinue study treatment permanently.                                                                                                                                                                 |

a. More conservative management is allowed if judged medically appropriate by the Investigator.

b. Participants requiring > 2 dose level reductions should discontinue protocol therapy permanently.

c. If toxicity returns to grade 0-1 after dose reduction, dose re-escalation is permitted at the discretion of the investigator.

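### Table 3 gives two differing instructions for a first Grade 2 skin event that does not improve; read cumulatively and without re-escalation, its third-occurrence row also asks for a dose level that does not exist

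*Protocol*

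**What the plan says.** All references are to the protocol.

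- **Section 7.2.1, Table 1.** The regorafenib row reads "Regorafenib | mg | 160 | 80 | 120 | 160": start 160 mg, level -1 is 120 mg, level -2 is 80 mg, and nothing lower.
- **Table 3, Grade 2, first occurrence.** The initial step is "Decrease dose by one dose level and immediately institute supportive measures". The row continues: "If there is no improvement, interrupt therapy for a minimum of 7 days, until toxicity resolves to Grade 0-1". It gives no dose for resumption.
- **Table 3, Grade 2, next row.** The trigger is "No improvement within 7 days or 2nd occurrence". The action is to interrupt until Grade 0-1, with no minimum length, and then: "When resume treatment, decrease dose by one dose level".
- **Table 3, Grade 2, third occurrence.** "Interrupt therapy until toxicity resolves to Grade 0-1. When resume treatment, decrease dose by one additional dose level". The row carries footnotes b and c.
- **Table 3, Grade 2, fourth occurrence.** Permanent discontinuation of study treatment.
- **Footnote b.** "Participants requiring > 2 dose level reductions should discontinue protocol therapy permanently".
- **Re-escalation, in three places.** Section 7.2 (dose reductions and delays) carries a specified reduction forward to every later dose. Footnote c, attached to the first three Grade 2 rows, allows re-escalation at the investigator's discretion once toxicity is back to Grade 0-1. The paragraph below Table 3 allows a return to the starting dose after one full cycle at the reduced dose without the reaction reappearing above Grade 1.

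**The concern.** A site with a first Grade 2 skin event that has not settled finds two rows that apply to it. They differ on whether a minimum interruption is required and on whether a further reduction is due. A site at the third occurrence finds a row that tells it to resume lower and a footnote on that row that may tell it to stop.

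The choice feeds several results that describe Arm B. Unacceptable toxicity as defined in section 7.2 is a ground for permanent discontinuation in section 7.4. Toxicity that ends study treatment is a treatment-failure event in section 13.2. Section 13.3 bases the interim compliance review on delivered dose, and section 14.2 asks the monitoring committee to watch drop-out for toxicity in the experimental arm. Skin toxicity is not a marginal case either: section 2 lists hand-foot syndrome at 20% for grade 3 or higher, second only to hypertension at 23%. If sites read the table differently, part of the apparent tolerability of the regimen will reflect that reading.

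**Working it through.** **1. Levels available.** Table 1 gives 160 to 120 to 80 mg, which is two reductions. This agrees with footnote b, which stops treatment beyond two. Table 1 and footnote b are therefore consistent with each other; the question is whether the Grade 2 rows fit them.

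**2. A first event that does not improve.** The two rows side by side:

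| | First-occurrence row | Next row |
|---|---|---|
| Minimum interruption | 7 days | none stated |
| Reduction | one level, made at once | one level, on resuming |
| Dose on resuming | not stated; 120 mg if silence means the dose already reduced | 80 mg if the cut is additional, 120 mg if it is the same cut |

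**3. Dose after each Grade 2 occurrence, with no re-escalation.**

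| Reading | 1st | 2nd | 3rd | Treatment stops at |
|---|---|---|---|---|
| A. Every reduction is additional, including the one for non-improvement | 120, then 80 mg | third reduction, no level | not reached | 2nd |
| B. Reductions add up across occurrences; non-improvement costs nothing more | 120 mg | 80 mg | third reduction, no level | 3rd |
| C. Levels are counted from the starting dose | 120 mg | 120 mg | 80 mg | 4th |

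Reading A applies only to a first event that fails to improve. A first event that improves follows B whenever reductions accumulate. The fourth-occurrence row is reached only under C.

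**4. Effect of re-escalation on readings A and B.** The paths were enumerated with no step up, one level up, or a return to start, before the second and before the third occurrence.

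- If the first event cost one reduction, any single re-escalation keeps the third-occurrence dose at 80 or 120 mg. For example, one level up before the second occurrence gives 120, 120, 80 mg.
- If the first event cost two reductions, the third-occurrence row stays within Table 1 only with a return to start before the second occurrence, or a re-escalation before both.
- Footnote b does not define its count. If it means levels below the start, re-escalation rescues the row as above. If it means every reduction ever made, these paths have made three reductions (reading B) or four (reading A) by the third occurrence, so it requires discontinuation even after re-escalation.

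**5. Grade 3 rows as a comparison.** They take one level, then one additional level under footnote b, then stop at the third occurrence. That is two reductions and fits Table 1. The Grade 2 rows use the same two phrases, but the first-occurrence row has already taken a level before they begin.

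**6. What the dose difference can do to the interim count.** One 21-day block is 160 x 21 = 3,360 mg, so two blocks are 6,720 mg. Assume that regorafenib is counted alone, block 1 is taken in full, and any interruption falls in the washout.

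- Block 2 at 120 mg: 3,360 + 2,520 = 5,880 mg, and 5,880 / 6,720 = 87.5%.
- Block 2 at 80 mg: 3,360 + 1,680 = 5,040 mg, and 5,040 / 6,720 = 75.0%.

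Section 13.3 counts patients who have not received more than 75%. The first patient is not counted and the second is. The margin is 5,880 - 5,040 = 840 mg, or seven days at 120 mg. If a seven-day interruption fell inside block 2, the first patient would also land on 75%. So the row chosen can change a patient's classification, but need not.

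**The case against.** The strongest defence is reading C. The Grade 3 rows use a ladder of one level, one additional level, then stop. Applied to Grade 2 with levels counted from the start, every row can be reached, Table 1 and footnote b are respected without re-escalation, and the first two rows give the same dose. The text allows this. It is not the plain meaning, though: an instruction to decrease by one level, given to a patient already reduced to 120 mg, reads as a move to 80 mg. Nothing in the table says that levels are counted from the start. What stands is that the defect is ambiguity, not impossibility.

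Three stronger statements are tempting, and the protocol does not support them.

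- A reader might infer that the table prints two resumption doses for one event. It does not. The first-occurrence row prints none, and 120 mg there is inferred from silence.
- A reader might infer that one row says resume while another says stop. The stop comes from footnote b, attached to the third-occurrence row itself as its limit. The fourth-occurrence row concerns a later event.
- A reader might infer that the third-occurrence row can never be carried out. Footnote c and the paragraph below Table 3 allow re-escalation, which can keep it workable. But re-escalation is discretionary, its terms differ between the three places, and a patient who was never re-escalated is still left with the problem.

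Other clauses do not settle the matter. The section 7.2 rule to take the longest delay and lowest dose covers several adverse events with differing recommendations, not one event under two rows. Footnote a allows more conservative management but does not say what the base instruction is. The two interruption rules can both be met by waiting at least seven days, which resolves the duration but not the dose.

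**Conclusion.** The point holds as a conflict of wording that should be corrected. Two Grade 2 rows govern the same non-improving first event with different instructions, leaving 120 or 80 mg open on resumption. If reductions are cumulative and the dose was not raised in between, the third-occurrence row asks for a third reduction that Table 1 cannot supply and footnote b turns into permanent discontinuation. Across the three readings, stopping falls at the second, third or fourth occurrence.

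The number of patients affected cannot be derived. The 20% in section 2 is for grade 3 or higher, where the rows fit Table 1, and the protocol gives no Grade 2 rate. Multiplying an assumed Grade 2 rate by the 38 Arm B patients would give only a ceiling, because just the non-improving or repeatedly recurring events reach the disputed text. The definition of the primary endpoint is not touched. What is exposed is the consistency across sites of delivered dose, the interim compliance count, time to treatment failure and the tolerability description of Arm B.

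**What to change.** The protocol authors should reconcile the Grade 2 rows of Table 3, footnotes b and c, Table 1, the carry-forward sentence in section 7.2 and the paragraph below Table 3, so that:

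- a first Grade 2 event that does not improve falls under one instruction, with one interruption rule and one statement on whether a further level is lost;
- each reduction is described either as additional to the current dose or as a level relative to the starting dose;
- footnote b says whether it counts levels below the start or all reductions made;
- re-escalation has one set of conditions;
- the sequence of occurrences fits the levels available and the discontinuation limit.

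Which sequence applies is for the clinical leads; no dose or stopping rule is proposed here. The cost is a table edit in a protocol amendment and a memo to sites, with no added procedures.

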## ALT GIST

|                                                                         |                |                                                                                                                                                                                                          |
|-------------------------------------------------------------------------|----------------|----------------------------------------------------------------------------------------------------------------------------------------------------------------------------------------------------------|
| participant to be unable to work or perform activities of daily living. |                | resolves to Grade 0-1. When resume treatment, decrease dose by one dose level.                                                                                                                           |
|                                                                         | 2nd occurrence | Institute support measures immediately. Interrupt therapy for a minimum of 7 days until toxicity resolves to Grade 0-1. When resume treatment, decrease dose by one additional dose level b . |
|                                                                         | 3rd occurrence | Discontinue study treatment permanently.                                                                                                                                                                 |

a. More conservative management is allowed if judged medically appropriate by the Investigator.

b. Participants requiring > 2 dose level reductions should discontinue protocol therapy permanently.

c. If toxicity returns to grade 0-1 after dose reduction, dose re-escalation is permitted at the discretion of the investigator.

**If there is no recovery after a delay of 28 days, treatment will be discontinued permanently.**

For participants who require a dose reduction for grade 2 or 3 rash or hand-foot skin reaction, the dose of study drug may be increased to the starting dose after one full cycle of therapy has been administered at the reduced dose without the reappearance of rash or hand-foot skin reaction > grade 1.

### ***7.2.2. Treatment-Emergent Hypertension***

The dose modification schedule for treatment-emergent hypertension during study drug dosing should be followed. Participants' Blood Pressure (BP) measurements will be monitored and appropriate treatment to effectively control hypertension is required.

(Table on next page).

# ALT GIST

Table 4:

| NCI-CTCAE v4.03 Grade | Definition                                                                                                                                                               | Anti-Hypertensive Therapy                                                                                                                                                                                                   | Regorafenib dosing                                                                                                                                                                                                                                                                                                                                                                                                                 |
|-----------------------|--------------------------------------------------------------------------------------------------------------------------------------------------------------------------|-----------------------------------------------------------------------------------------------------------------------------------------------------------------------------------------------------------------------------|------------------------------------------------------------------------------------------------------------------------------------------------------------------------------------------------------------------------------------------------------------------------------------------------------------------------------------------------------------------------------------------------------------------------------------|
| Grade 2               | Systolic BP 140-159 mmHg or diastolic BP 90-99 mmHg
OR
Symptomatic increase by > 20 mmHg (diastolic) if previously within normal limits                            | Treat with the aim to achieve diastolic BP $\leq$ 90 mmHg
- If BP previously within normal limits, start anti-hypertensive monotherapy
- If participant already on anti-hypertensive medication, titrate up the dose. | Continue regorafenib.
If symptomatic, hold regorafenib until symptoms resolve AND diastolic BP $\leq$ 90 mmHg a .
When regorafenib is restarted, continue at the same dose level                                                                                                                                                                                                                                  |
| Grade 3               | Systolic BP $\geq$ 160 mmHg or diastolic BP $\geq$ 100 mmHg
OR
More than one anti-hypertensive medication or more intensive therapy than previously used indicated | Treat with the aim to achieve diastolic BP $\leq$ 90 mmHg
- Start anti-hypertensive medication
AND/OR
- Increase current anti-hypertensive medication
AND/OR
- Add additional anti-hypertensive medications. | Hold regorafenib until diastolic BP $\leq$ 90 mmHg, and if symptomatic, until symptoms resolve a .
When regorafenib is restarted, continue at the same dose level
If BP is not controlled with the addition of new or more intensive therapy, reduce by 1 dose level b .
If Grade 3 hypertension recurs despite dose reduction and antihypertensive therapy, reduce another dose level c |
| Grade 4               | Life-threatening consequences (e.g. malignant hypertension, transient or permanent neurologic deficit, hypertensive crisis)                                              |                                                                                                                                                                                                                             | Discontinue study treatment permanently                                                                                                                                                                                                                                                                                                                                                                                            |

a. Participants requiring a delay of 28 days will be permanently discontinued.

b. If blood pressure remains controlled for at least one full cycle, dose re-escalation is permitted at the Investigator's discretion.

c. Participants requiring > 2 dose level reductions will be permanently discontinued.

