## 7.3.5. Concomitant medication reporting

Concomitant medications will not be recorded during the study, except for medications being taken at the onset of serious adverse events or medications known to interact with the study medications.

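### Table 4 gives opposite regorafenib instructions for an asymptomatic patient already on an antihypertensive whose diastolic pressure is about 91–99 mmHg

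*Protocol*

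**What the plan says.** Table 4 in section 7.2.2 governs regorafenib dosing for hypertension in Arm B.

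- **Grade 2** is "Systolic BP 140-159 mmHg or diastolic BP 90-99 mmHg", or a symptomatic diastolic rise of more than 20 mmHg from normal. For a patient already treated: "If participant already on anti-hypertensive medication, titrate up the dose". For regorafenib: "Continue regorafenib", with the exception "If symptomatic, hold regorafenib until symptoms resolve AND diastolic BP $\leq$ 90 mmHg". Restart is at the same dose level.
- **Grade 3** is systolic pressure of at least 160 or diastolic of at least 100 mmHg, or "More than one anti-hypertensive medication or more intensive therapy than previously used indicated". The two parts are joined by OR, and the second carries no pressure limit. For regorafenib: "Hold regorafenib until diastolic BP $\leq$ 90 mmHg, and if symptomatic, until symptoms resolve". Then: "If BP is not controlled with the addition of new or more intensive therapy, reduce by 1 dose level", with a further level if Grade 3 recurs.
- **Footnotes** end treatment permanently for a delay of 28 days or a need for more than two dose-level reductions.

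Three other sections bear on the point. Section 7.2 has a general rule to withhold treatment for Grade 3–4 events unless otherwise specified, and a tie-break for a patient with several adverse events. Section 9.5 grades adverse events by worst CTCAE v4.03 grade. Section 7.3.5 states: "Concomitant medications will not be recorded during the study, except for medications being taken at the onset of serious adverse events". It makes a second exception for drugs known to interact with the study drugs.

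**The concern.** Each row of a dose-modification table should capture patients that no other row captures, or the table should say which row wins. Here the action that the Grade 2 row prescribes for an already-treated patient is itself a criterion for Grade 3. The Grade 3 therapy cell confirms this, because increasing the current antihypertensive is one of its listed options. The same patient can therefore be read into two rows that disagree about regorafenib.

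Such patients can enrol. Exclusion criterion 9 removes only those whose pressure stays above 140 systolic or 90 diastolic despite optimal management, so treated and controlled hypertension is allowed.

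What is at stake is consistent dosing between sites. Only the Grade 3 row leads to dose reduction, and repeated reductions end treatment. The reading a site adopts can therefore affect the dose-intensity check in 13.3 and, through discontinuation, time to treatment failure (9.4, 13.2).

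**Working it through.** No stated figure is to be reproduced. The check applies both rows of Table 4 to a patient already on an antihypertensive whose pressure is in the Grade 2 range and below the Grade 3 pressure thresholds. Titrating the antihypertensive up, as Grade 2 instructs, satisfies the second part of the Grade 3 definition in every case.

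| Already-treated patient | Grade 2 row | Grade 3 row (therapy criterion) | Result |
|---|---|---|---|
| No symptoms, diastolic 91–99, systolic below 160 (e.g. 148/94) | Continue regorafenib | Hold until diastolic is 90 or below | Opposite instructions |
| No symptoms, systolic 140–159, diastolic 90 or below | Continue | Hold, but the restart condition is already met | Two grades; the hold has little or no effect |
| Symptomatic, Grade 2 range | Hold until symptoms resolve and diastolic is 90 or below | Same hold | Same hold; two grades; only Grade 3 leads on to dose reduction |

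A previously untreated patient who starts a single drug is assigned to Grade 2 by name and is outside this point.

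**Is there a tie-break?** Table 4 has none. The rule in 7.2 that selects the longest delay and lowest dose is written for several adverse events with different recommendations, not for one event that meets two grade definitions. The general Grade 3–4 withholding rule applies only once the event has been called Grade 3, which is the question.

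**What the choice of row can change.** Two cycles of regorafenib are 2 × 21 = 42 dosing days. Section 8.2.2 schedules blood pressure weekly in this period, so take a hold of one monitoring interval, 7 days. If held days are not made up (7.1 says missed tablets cannot be compensated for), one such hold costs 7/42 = 16.7% of planned regorafenib and two cost 14/42 = 33.3%. One dose level down is 120/160 = 75%, which is not more than the 75% criterion in 13.3. These figures assume that 13.3 is applied to regorafenib on its own, which it does not state. They show only that the row chosen can matter to that check.

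**How many patients?** The count needs the proportion of Arm B on antihypertensives and, among those, the proportion who reach an asymptomatic diastolic pressure of 91–99 below the Grade 3 pressure thresholds. The protocol gives neither. A patient who starts an antihypertensive during the study and later returns to that range would also qualify.

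**The case against.** The strongest reply is that the stricter reading is implied: 9.5 asks for the worst grade, and 7.2 leans toward withholding. This stands in part. Worst-grade reporting goes a good way toward settling which grade is tabulated, so a reader who infers that the reported Grade 3 rate is arbitrary goes further than the documents allow. It does not settle dosing. If Grade 3 always prevailed, the Grade 2 instruction for already-treated patients would never govern the patients it names, and the table would still need correcting.

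A second reply is that the Study Manual, which is not shown, may clarify management; 8.2.2 says it will carry antihypertensive recommendations. It may, but 7.2.2 tells sites to follow the schedule in the protocol, and a manual does not remove a contradiction there.

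Three stronger readings are tempting and not supported:

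- *Every treated patient faces opposite instructions.* The table above shows that continue and hold conflict only without symptoms and with diastolic pressure of about 91–99.
- *About 8 to 15 of 38 patients are affected.* This comes from assuming that 20% to 40% enter on antihypertensives (0.20 × 38 = 7.6; 0.40 × 38 = 15.2), and it counts everyone on treatment rather than those who reach the conflict. If, again by assumption, 25% to 50% of them reach it, the result is 1.9 to 7.6. Nor does the 23% Grade 3 or higher rate cited in section 2 (0.23 × 38 = 8.7) help: it is an overall rate from an earlier trial in patients who had failed at least two lines, not a rate of ambiguous cases.
- *The recording rule in 7.3.5 is an error.* The protocol plans no central regrading and calls the trial pragmatic, sites keep source records, and Table 4 does not govern Arm A. Limited medication capture is a legitimate choice.

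**Conclusion.** The contradiction holds as written, within limits. An Arm B patient already on an antihypertensive, asymptomatic, with diastolic pressure of about 91–99 mmHg and systolic below 160, is told by one row of Table 4 to continue regorafenib and by the next to hold it, and nothing in the protocol ranks the rows for a single event. The conclusion rests on one reading: that raising a dose counts as more intensive therapy than previously used. The Grade 3 therapy cell supports it.

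The number affected cannot be derived from the documents. It is mainly some fraction of the Arm B patients who enter on antihypertensives. The consequence is inconsistent holds and reductions, with possible effects on dose intensity and discontinuation. Tumour response, the primary endpoint, is not directly touched.

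As a secondary observation, 7.3.5 means that therapy-based grades generally cannot be checked from the trial database, because hypertension managed by titration would not ordinarily be a serious event. That limits verification and is not a fault in itself. This review does not judge which of the two clinical instructions is right.

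**What to change.** Reconcile the Grade 2 and Grade 3 rows of Table 4 so that each combination of pressure, symptoms and background antihypertensive therapy leads to exactly one regorafenib instruction. The sponsor chooses which. Keep reported grades on CTCAE v4.03 as in 9.5; only the dosing instruction needs to be made unique. Check that the Study Manual's hypertension guidance then says the same.

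The cost is a few lines of table wording in an amendment, which under 15.3 needs the International Steering Committee and ethics approval. Sample size, endpoints and data collection are unchanged. No medication log or central regrading is needed for this point.
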